## Measuring instruments

### Primary outcomes

#### Mental health of children

The CBCL 6/18 assesses behavioral problems, emotional problems, somatic complaints, and social competencies of school-aged children and adolescents from the parents' perspective (94, 95). The eight problem scales can be aggregated into internalizing and externalizing disorder scales and a total score. The German manual reports adequate internal consistencies for the total problem score and the internalizing and externalizing scales, with Cronbach's *α* > .80.

The YSR/11-18R, derived from the CBCL/6-18, captures competencies and problems of adolescents aged 11–18 years, similar to the CBCL/6-18, but uses a self-report measure (94). The translated version from Döpfner and colleagues was used (95). The internal consistency of the total problem score is very high (Cronbach's *α* ≥ .93), while the internalizing and externalizing behavior scales demonstrate good reliability (Cronbach's *α* > .80).

#### Maternal distress

The short form of the DASS-21, adapted via forward-backward translation, is used to assess negative emotional states based on their frequency over the past four weeks (1 = “never” to 4 = “very often”) (96). The DASS-21 includes three dimensions: depression (e.g., dysphoria and hopelessness), anxiety (e.g., autonomic arousal and situational fear), and stress (e.g., chronic, nonspecific arousal and irritability).

#### Child maltreatment and neglect

The CTS-PC, adapted via forward-backward translation, is the parent-child version of the CTS and measures psychological and physical maltreatment, neglect, and non-violent discipline of children by parents (99). In the present studies, 31 items were used in the mothers' interviews and 16 items in the children's interviews. The CTS-PC captures the subscales Non-Violent Discipline, Psychological Aggression, Physical Assault, and Neglect.

The MNBS, whose German version was developed as part of the LIFE study at the University of Leipzig, is an instrument for assessing various forms of parental behavior related to child neglect (98). Different versions of the MNBS exist, all of which measure the extent to which the following needs of the child have been neglected: physical needs (e.g., food and clothing), emotional needs (e.g., affection and support), supervisory needs (e.g., addressing misbehavior and knowing the child's whereabouts), and cognitive needs (e.g., reading or helping with homework). The MNBS is available as a self-report measure for parents of children aged 0–15 years (Form P/PS). In the present study, eight items were presented to both mothers and children.

### Secondary outcomes

#### Dysfunctional parenting behavior

The short form of the Parenting Scale (PS) is a measure designed to assess dysfunctional parental disciplinary practices (100, 101). Based on a child behavior scenario, parents are asked to rate their own behavior between a functional and a dysfunctional approach. Two subscales—overreactivity (mothers: *α* = 0.77) and laxness (mothers: *α* = 0.73)—as well as a total score (mothers: *α* = 0.79) can be calculated.

#### Children's life satisfaction

The Inventory for Assessing the Quality of Life in Children and Adolescents (ILK) is a tool for measuring the quality of life in children and adolescents (102). The quality of life is divided into different domains, which are separately assessed in the ILK: school, family, peer relationships, and interests and leisure activities. Additionally, two health-related domains—physical health and mental health—are included. Beyond the individual domains, an overall assessment of quality of life is also provided. The internal consistencies of the quality-of-life score, based on child and adolescent self-reports, range between Cronbach's *α* = .55 and .63.

#### Mothers' life satisfaction

The Short Form of the Questionnaire for Life Satisfaction (FLZ) is designed to measure relevant aspects of life satisfaction in mothers across various life domains, such as health, financial situation, leisure time, relationship with their own children, or housing (103). In addition to assessing domain-specific life satisfaction, the FLZ allows for the estimation of general life satisfaction, calculated as the sum of seven out of the ten scales. The internal consistency for the total score is satisfactory (Cronbach's *α* = .74 for mothers). The FLZ has been normed on a representative German sample, with additional norms available for various age and occupational groups.

#### Child's consumption of alcohol, cigarettes, and Cannabis

The frequency of alcohol, cigarette, and cannabis consumption is assessed using questions from the Lower Saxony Survey 2019 (104).

#### Parent-teenager conflicts

The Conflict Behavior Questionnaire (CBQ-20; adapted via forward-backward translation) is a 20-item self-report instrument designed to assess perceived conflict and communication behavior between parents and children from the mothers' perspective (CBQ-E version). The items refer to the past two weeks and are answered with “true” (agreement) or “false” (disagreement). The results of the CBQ-20 correlate at .96 with the longer version of the CBQ, which contains 73 items (105) and has demonstrated high internal consistency (106).

#### Academic performance of children

Data referring to current school type, grade repetition, educational aspirations, current grades in German, English, and Mathematics is collected.

#### Child's criminal behavior

Criminal and violent behavior are assessed using questions from the Lower Saxony Survey 2019 (104). Criminal behavior is measured with 9 items. Example items include: “Have you ever deliberately stolen something from a shop, department store, or store?” Violent behavior is assessed with 6 items. Example items include: “Have you ever demanded money or possessions (e.g., a jacket, watch, shoes) from someone and seriously threatened violence if they did not hand them over or pay?” In addition, data from the BZR for the ProKind children's/adolescents' cohort will be gathered. These data include information on criminal convictions and relevant judicial decisions.

#### Mortality rate

Data from the EMA will be obtained to assess mortality rates.

#### Social benefit receipt

The IAB provides comprehensive data on integrated employment biographies as well as data from the SGB II performance statistics, accessed via the IAB's sampling frame (LST-S).

#### Subsequent pregnancy and desire for children

In line with previous surveys in the ProKind project and as a continuation, mothers are asked about their current family life and future family planning. This includes questions regarding contraception methods or an (already realized) additional desire for children. Administrative data further allow the tracking of how many subsequent children the mothers have had. In addition, adolescents from the ProKind cohort are asked about experiences with pregnancies and births. Administrative data further allows the identification of whether adolescents of the child cohort have already become parents.

## Data analysis

The primary and secondary analyses will be conducted on an intention-to-treat basis. We will standardize and recode all continuous outcomes such that positive values correspond to beneficial effects. The reported effect sizes (ESs) will be interpreted as group differences in standard deviations (SDs) of the CG. Confidence intervals (CIs) for the ESs will be obtained using bootstrap methods with 5,000 replications. One-sided tests (*p* < .05) will be conducted under the assumption that the intervention is not harmful.

Following the analytic strategy used in the 7yrs-fu of ProKind (41), as well as in recent evaluations of the trial (42, 71), to address missing observations from families who did not participate in the follow-up and to account for the imbalance in a few baseline risk factors (e.g., maternal aggression and mental health problems) between IG and CG, treatment effects will be estimated using augmented inverse probability weighting (AIPW) in combination with the “least absolute shrinkage and selection operator” (lasso) to select relevant control and weighting variables (107).

The AIPW technique assigns weights to observed cases based on the inverse of their probability of loss to follow-up estimated by logit functions, thereby mitigating potential selection bias caused by attrition. In a second step a linear weighted function with additional control variables is estimated. The variables used in the logit functions for the weighting and the control variables for the linear weighted function are selected by lasso, a machine learning algorithm. By weighting participants according to their inverse probability of remaining in the study, the analytic sample is reweighted to more closely resemble the original randomized population, thereby improving both internal validity and generalizability of the findings. Due to findings of the last program phase, all primary and secondary outcomes will be analyzed regarding any differential effects, while controlling for children's gender (41) and delivery model (42).

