Consistent with the second phase of the ProKind study, information is collected regarding prior employment, periods of unemployment, welfare receipt, participation in qualification programs during unemployment, and employment details from the Technical Data Center (FDZ) of the IAB in Nuremberg, which is part of the German Federal Employment Agency. Participants had the option to provide self-reported data but withhold permission for researchers to access administrative data. Furthermore, the data linkage with the EMA allows access to official records on mortality of both children and mothers as well as on further births of the participating mothers and their children. Regular inquiries are made to the Federal Central Criminal Register (Bundeszentralregister, BZR). This register records criminal convictions by German courts, certain decisions by administrative authorities, notes on incapacity to be held criminally responsible, and special judicial determinations, as well as subsequent decisions and facts related to these entries. When the relevant conditions are met, foreign convictions of German nationals or individuals born or residing in Germany are also entered into the register. An anonymized report for scientific research purposes is unrestrictedly possible.

Power analyses indicated that with a one-sided test at *α* = .05 and statistical power of 1–*β* = .80, the trial is adequately powered to detect small effects. Calculations were based on the original allocation proportions of the study (*n* = 394 in the IG and *n* = 361 in the CG). Three scenarios were considered. Scenario 1 assumes administrative data with an expected re-engagement of 93% (*n* ≈ 700) which allows the detection of effects of at least ES = 0.19. Scenario 2 assumes a response rate of about 70% (*n* ≈ 530) as observed in the 7yrs-fu (41) which allows the detection of effects of at least ES = 0.22. Scenario 3 assumes a more conservative retention rate of 60% (*n* ≈ 450) which allows the detection of effects of at least ES = 0.23. According to Cohen (93), these values correspond to small effect sizes.

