Third, the high loss to follow-up during the initial project phase, with rates of about 55% by the 24-month assessment (54), which is substantially above the commonly recommended 20% threshold for RCTs. Such high attrition rates limit the generalizability of the findings, as selective participation may bias estimates toward more resilient or resourceful families and reduce confidence in the representativeness of the intervention effects. This also complicates the interpretation of long-term outcomes, since early selective loss may systematically affect which families remain available for later follow-up assessments. In contrast, retention improved considerably in the 7yrs-fu, with response rates of about 70% in both groups (41). Importantly, in this later phase advanced statistical methods were applied, including inverse probability weighting (IPW). In this procedure, the probability of remaining in the study was modeled using baseline characteristics such as maternal age, socioeconomic status, partnership status, and mental health indicators. Participants who shared characteristics with those lost to follow-up received higher weights in the analysis, thereby reducing selection bias. IPW thus not only improves internal validity but also tackles the problem of generalizability, as it makes the analytic sample more closely resemble the original randomized population. This marks a significant methodological improvement compared to Phase I and will strengthen the robustness and validity of future findings. Nevertheless, even with such procedures, some degree of residual bias cannot be entirely ruled out in long-term evaluations.

Fourth, the widespread availability of German midwifery care in the CG represents an important contextual factor. Using health insurance data, Sandner et al. (68) demonstrated that around 70% of mothers in the CG made use of at least one statutory midwifery visit. It is therefore conceivable that this high baseline level of standard care may have attenuated the likelihood of detecting additional program effects in domains such as maternal physical health or breastfeeding outcomes.

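### The Data analysis section defines the attrition weight in two incompatible ways, and the first definition (inverse probability of loss) is inverted

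*Protocol article*

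**What the plan says.** The Data analysis section of the protocol article estimates treatment effects by augmented inverse probability weighting (AIPW) with lasso selection of variables, partly to deal with families who do not take part in the follow-up. It then describes the weight twice in one paragraph.

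- First description: "The AIPW technique assigns weights to observed cases based on the inverse of their probability of loss to follow-up estimated by logit functions". The sentence goes on to say that this reduces selection bias from attrition.
- Outcome step: "In a second step a linear weighted function with additional control variables is estimated".
- Second description, three sentences after the first: "By weighting participants according to their inverse probability of remaining in the study", with the stated result that "the analytic sample is reweighted to more closely resemble the original randomized population".

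The same section says that the approach follows the one used at the 7-year follow-up. The Limitations section describes that earlier weighting: "the probability of remaining in the study was modeled using baseline characteristics", and "Participants who shared characteristics with those lost to follow-up received higher weights in the analysis".

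**The concern.** Inverse probability weighting for attrition works because each responder stands in for similar families who were lost. A responder with a low chance of being observed must therefore count for more, which means a weight of 1/P(observed). A weight of 1/P(loss) does the opposite: a responder who closely resembles the dropouts gets a small weight, and a family almost certain to stay gets a very large one.

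The inverted sentence is the one that introduces the technique and its logit model, so it is a natural place for a programmer or replicator to start. The weight feeds the effect estimates. The power section (under Procedure and re-engagement strategy) plans for response of about 70% or 60% where administrative data are not used, so 30% to 40% of families could be missing for the interview and questionnaire outcomes, which include all the primary ones. The Limitations section itself names selective loss as a threat and points to weighting as the main remedy. The article states this definition rather than leaving it to an analysis plan, so it should be right.

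**Working it through.** The document gives no figure that depends on the weight, so there is nothing to reproduce. The check is of direction and consistency, followed by an illustration.

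**Direction.** Let p = P(remaining), so P(loss) = 1 − p.

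- 1/p falls as p rises: likely leavers who respond are weighted up.
- 1/(1 − p) rises as p rises: likely stayers are weighted up.

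The two rules order the families in opposite ways, so they cannot both be meant.

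**Consistency of the text.**

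| Place | Implied weight |
|---|---|
| Data analysis, first description | 1/P(loss) |
| Data analysis, later sentence | 1/P(remaining) |
| Data analysis, aim of resembling the randomised population | 1/P(remaining) |
| Limitations, 7-year method (dropout-like families weighted up) | 1/P(remaining) |

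Only the first is out of line.

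**Illustration of the covariate mix.** Overall retention of 70% is taken from Scenario 2 of the power section; the 7-year follow-up achieved (274 + 258)/755 = 70.5%. The rest is assumed, not from the document: half of the families are high-risk, and retention in low-risk/high-risk families is 90%/50%, 85%/55% or 80%/60%, each averaging 70%. The weighted high-risk share among responders is

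p_h·w_h / (p_l·w_l + p_h·w_h), with a target of 50%.

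For 90%/50%:

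- Unweighted: 0.50/(0.90 + 0.50) = 35.7%.
- 1/P(remaining), weights 1.111 and 2: 1.00/(1.00 + 1.00) = 50.0%.
- 1/P(loss), weights 10 and 2: 1.00/(9.00 + 1.00) = 10.0%.

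| Assumed retention (low/high risk) | Unweighted | 1/P(remaining) | 1/P(loss) |
|---|---|---|---|
| 90% / 50% | 35.7% | 50.0% | 10.0% |
| 85% / 55% | 39.3% | 50.0% | 17.7% |
| 80% / 60% | 42.9% | 50.0% | 27.3% |

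In every case the inverted weight is further from the target than no weighting, and the correct weight restores the target exactly.

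**From covariate mix to treatment effect.** This step is less certain. Simulations used 394 and 361 randomised, 70% retained, a retention log-odds slope of 0.8 per SD of baseline advantage, and a mean effect of 0.20 SD. The slope and the effect are assumptions.

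- Effect constant across families, same retention slope in both arms: the inverted weight still gives 0.20.
- Effect assumed to shrink by 0.15 SD per SD of advantage, weights only: complete cases give 0.17, 1/P(remaining) gives 0.20 and 1/P(loss) gives 0.08.
- Same heterogeneity, with the covariate added as a common main effect in the weighted regression: 1/P(loss) still gives 0.08.
- Same heterogeneity, with separate outcome models by arm averaged over all 755 families: 1/P(loss) gives 0.20, with some loss of precision.

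The inverted weight therefore reliably worsens the sample mix. It biases the effect only under some combinations of heterogeneity and outcome model.

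**The case against.** The strongest reply is that the correct definition is already in the plan. The later sentence, the stated aim and the 7-year precedent all point to 1/P(remaining), and an analyst who knows the method would read the first sentence as a slip. Nothing in the article suggests that inverted weights have been or will be programmed. The plan also has an outcome-model step, which in its usual augmented form can protect the estimate when the weight model is wrong.

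Most of this stands. A reader might infer from the first sentence that the planned analysis enlarges attrition bias. The documents do not support that: it would require the slip to be coded against the rest of the text, and then effects that vary with the factors driving attrition (or attrition that differs by arm), together with an outcome model that does not absorb this.

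Two parts do not stand. The outcome model cannot be counted on as a safeguard, because the article describes only a weighted linear function with controls. With a common main effect, that form did not remove the bias under the assumed heterogeneity. And a definition that can be recovered only by overruling the sentence that first states it still needs correcting, because it belongs to the main estimator.

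**Conclusion.** The point holds as an internal contradiction in the definition of the primary analysis. One of the two weight definitions in the paragraph is wrong, and the text makes clear which. Coded literally, it would take the high-risk share among responders to between 10.0% and 27.3%, against a target of 50% and 35.7% to 42.9% unweighted. Those figures rest on an assumed even split of risk strata and on the three assumed retention patterns.

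The size of any bias in the treatment effect cannot be fixed from the document. It ranges from none to more than half of an assumed 0.20 SD effect (0.08 estimated), depending on assumptions that the article does not settle, so the simulated effects are illustrations only. This is a low-cost correction and not evidence that the trial's analysis will be biased.

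**What to change.** In the first description of the weight in the Data analysis section, replace *probability of loss to follow-up* with *estimated probability of remaining in the study (outcome observed)*. The sentence then agrees with the later one and with the Limitations section. Before analysis, confirm that the code uses weight = 1/P(observed). A simple check is that the weighted baseline means of responders move towards those of all 755 randomised women. The cost is one sentence and one code check, with no change to the design, the data or the intended method.

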## Sample at baseline and randomizations procedure

At the time of baseline data collection (2008–2009), women in the 12th to a maximum of the 28th gestational week were recruited based on the following inclusion criteria: (a) an ongoing pregnancy (<28 weeks), (b) at least one financial risk factor [e.g., receipt of unemployment benefits (ALG II), debt], (c) at least one additional social or personal stress factor (e.g., being underage, lack of a school diploma, personal experiences of abuse or neglect) and (d) at least basic knowledge of the German language to enable communication with the German-speaking family companions (≙ A1–A2 language level). Participants were recruited through various intermediaries, including gynecologists, midwives, youth welfare offices, psychosocial counseling centers, and employment agencies. In total, *N* = 1.157 interested pregnant women registered to participate in the project. Of these, *n* = 263 did not meet the inclusion criteria, and *n* = 139 declined participation after receiving detailed information about the project. The final sample of *N* = 755 women was randomly assigned to an intervention group (IG, *n* = 394) or a control group (CG, *n* = 361) using Efron's Biased Coin Design (62), stratified by municipality (urban vs. rural), age (≤18 vs. >18 years), and maternal nationality (German vs. non-German). The women were, on average, 21 years old at the start of the project; approximately 88% were unmarried (about 28% were single parents), and about 12% had a migration background. Only about 18% reported that the current pregnancy was unwanted. The CG did not receive any study-related interventions but had access to the regular services of the German healthcare system (*treatment as usual*, TAU). This includes the statutory right to midwifery care during pregnancy, childbirth, and the postpartum period, as enshrined in the German Midwifery Act (HebG) and the Midwifery Training and Examination Regulation (HebAPrV).

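### Lasso picks the variables of both models, so neither is guaranteed to contain the baseline imbalances the plan wants to adjust for, or the randomisation strata

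*Protocol article*

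**What the plan says.** The section on the baseline sample describes allocation by Efron's biased coin, "stratified by municipality (urban vs. rural), age (≤18 vs. >18 years), and maternal nationality (German vs. non-German".

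The Data analysis section gives two reasons for its estimator. One is non-participation at follow-up. The other is "to account for the imbalance in a few baseline risk factors (e.g., maternal aggression and mental health problems) between IG and CG". It then states that "treatment effects will be estimated using augmented inverse probability weighting (AIPW) in combination with the" lasso. Selection applies to both parts of the estimator: "The variables used in the logit functions for the weighting" are chosen by lasso, and so are the "control variables for the linear weighted function are selected by lasso, a machine learning algorithm".

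No variable is named as always retained in the main analysis, and the strata are not mentioned in this section. The only covariates named as controlled for belong to the differential-effects analyses: "while controlling for children's gender (41) and delivery model (42".

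**The concern.** The plan names variables that it must account for and then makes their inclusion depend on an algorithm that may discard them. This is a stated rule, not a detail left open, and the rule does not guarantee its own stated purpose.

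Lasso keeps strong predictors and tends to drop modest ones. A modest predictor that differs between arms still shifts the treatment estimate when it is left out. The logit, as described, models loss to follow-up, so its weights target attrition. Correcting a between-arm imbalance then falls mainly to the outcome model. Tests are one-sided, so a bias towards the intervention translates directly into false positives.

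For the strata the issue is different. The article never says the model is meant to adjust for them. The point there rests on the general principle that an analysis should reflect a stratified allocation.

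**Working it through.** **Inputs from the article.** Allocation is 394 : 361, with a one-sided alpha of 0.05 and power of 0.80. The scenarios are n ≈ 700, 530 and 450, with detectable effects of 0.19, 0.22 and 0.23 (Procedure and re-engagement strategy).

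**Reproducing the plan's figures.** At n = 530 the arms are 530 × 394/755 = 276.6 and 253.4.

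- SE = √(1/276.6 + 1/253.4) = 0.087.
- Detectable effect = (1.645 + 0.842) × 0.087 = 0.216, against 0.22 stated.
- The other two scenarios give 0.188 and 0.235, against 0.19 and 0.23.

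The power statement holds as an unadjusted two-group comparison. It supplies the standard error used below but does not bear on covariate selection.

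**Assumptions (not in the article).** Arm imbalance of 0.2 SD; 30 candidate covariates; two other predictors with slope 0.2; unit residual variance; prognostic slopes of 0.05 to 0.20 SD per SD; a single outcome lasso without attrition weights; 120 runs per slope, so drop rates carry a Monte Carlo standard error of up to about 5 percentage points (√(0.25/120) = 0.046).

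**Formulas.** Bias if dropped = slope × imbalance. One-sided error if dropped = 1 − Φ(1.645 − bias/0.087), for a bias favouring the intervention and given the observed imbalance.

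| Slope | Dropped, plug-in penalty | Dropped, cross-validation | Bias if dropped (SD) | One-sided error if dropped |
|---|---|---|---|---|
| 0.05 | 100% | 61% | 0.01 | 6% |
| 0.10 | 92% | 27% | 0.02 | 8% |
| 0.15 | 70% | 4% | 0.03 | 10% |
| 0.20 | 27% | 0% | 0.04 | 12% |

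For example, at slope 0.10: 1.645 − 0.02/0.087 = 1.415, and 1 − Φ(1.415) = 0.079. At slope 0.20: 1.645 − 0.04/0.087 = 1.185, and 1 − Φ(1.185) = 0.118.

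**Averaged over selection.** The last two columns apply only when the factor is dropped. Multiplying bias by drop rate gives an average of 0.010, 0.018, 0.021 and 0.011 SD down the table with the plug-in penalty, and 0.006, 0.005, 0.001 and 0 with cross-validation. In the simulation, the plug-in estimate minus the estimate with the factor forced in was 0.011, 0.017, 0.019 and 0.008, which agrees.

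**Sensitivity.** With 50 candidates and a plug-in penalty, a slope of 0.15 was dropped in 58% or 69% of runs at n = 530, depending on how the noise scale enters the penalty. If the outcome model were fitted separately by arm (the control arm has about 253), the 58% rose to 90%.

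**Strata.** Take a binary factor with 12% prevalence (the article's share with a migration background, as a stand-in for nationality) and an assumed effect of 0.3 SD. It explains 0.3² × 0.12 × 0.88 = 0.0095 of unit outcome variance. Including it multiplies the standard error by √(1 − 0.0095) = 0.995, a gain of about 0.5%.

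**The case against.** Several counter-arguments have force.

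- **A larger bias might be inferred.** A reader could take a slope of 0.3 with a 0.2 SD imbalance and get 0.06 SD, about a quarter of the 0.22 detectable effect. Lasso seldom produces that case. With 50 candidates and a plug-in penalty, a slope of 0.3 was dropped in under 1% of runs at n = 530, and in 10 to 25% at n = 253 depending on the setup. The factors at risk are the weaker ones.
- **The drop rates hang on unstated settings.** Neither the penalty nor the candidate list is given. With cross-validation the problem nearly disappears from slope 0.15 upwards. This stands, which is why a range is shown.
- **The simulation is not the planned estimator.** A factor missed by one AIPW model may be picked up by the other. Compensation may be partial, so the figures are conditional illustrations, not forecasts.
- **The strata matter less than they may seem.** One might infer that leaving them out invalidates the standard errors. Omitting a balanced stratum instead makes them conservative and costs little precision. That changes only if the 30 to 40% non-response in scenarios 2 and 3 unbalances the strata.
- **Retention could be settled elsewhere.** The article follows the strategy of the 7-year follow-up, whose weighting variables (Limitations) included maternal age and mental health indicators. That describes an earlier phase and does not bind this one. A separate analysis plan could force variables in, but the article's wording assigns both sets to lasso without exception.

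Nor is it right that every covariate is left to lasso: child gender and delivery model are named for the differential-effects analyses.

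**Conclusion.** The point holds and should be acted on, at moderate size. As written, neither model is guaranteed to contain the imbalanced risk factors that motivate the adjustment, or the three strata.

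Where a factor with slope 0.10 to 0.20 is dropped, the remaining bias is about 0.02 to 0.04 SD. If it favours the intervention, the one-sided error is about 8 to 12% instead of 5%. This rests on an assumed 0.2 SD imbalance, since the article gives neither its size nor its direction, and it ignores compensation by the other AIPW model. The article speaks of a few imbalanced factors, so biases could add or cancel.

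The documents do not show that these factors will be dropped, only that nothing prevents it. For the strata the expected loss is slight precision, unless attrition unbalances them.

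**What to change.** State in the Data analysis section that the three stratification factors (municipality type, age group, nationality) and the named imbalanced baseline variables (maternal aggression, mental health problems) enter unpenalised in both the response logit and the outcome model, for every outcome. Lasso then chooses only among the remaining baseline variables.

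This sets the drop probability of these variables to zero and keeps the core adjustment the same across outcomes. It costs one sentence, an option in the lasso call, and about 5 to 6 degrees of freedom out of about 530. Resampling the bootstrap within strata is not required: no gain from it has been shown, and the biased coin did not fix counts within strata.
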